#### Index crisis episode

Conducting an ITS that includes a time-dependent outcome—in this case a routine care episode, acute care episode, housing assessment, or jail entry within 30 days following a crisis episode—requires defining an index crisis episode to start the clock for the outcome time interval. Furthermore, given that there may be multiple index episodes per unique individual, the index crisis episode needs to be defined per ITS interval, which, based on our preliminary power analysis, will be divided as one calendar month per interval. The index crisis episode will therefore be defined as the first instance in a given month that an individual has a crisis episode, with the 30-day post-crisis outcome period trailing the end date of the index episode.

We also need to account for the fact that a single crisis episode may result in multiple contacts with different settings in the acute behavioral health care system. To account for this variability, we will use our clinical knowledge of common care pathways as the basis for a crisis system map (Fig 2) that defines different sequences of care as either a step-up in service intensity (e.g., mobile crisis followed by crisis stabilization or ED), a step-down in service intensity (e.g., PES followed by crisis stabilization), or a distinct crisis episode that mostly likely signifies reutilization (e.g., PES followed by mobile crisis, or two consecutive mobile crisis episodes). We will then combine sequences with a step up or down in service intensity that occur within two or fewer days between the end of the first and start of the second clinical setting, so as not to miscount these care transitions as reutilization. This approach also allows us to create a variable describing these crisis system trajectories, thus allowing us to identify potential differences between index crisis episodes based on crisis system entry point and end point. All crisis services utilized three or more days after the index crisis episode end date will be considered separate from the index crisis episode.

#### Outcome variables

We will build ITS models using the following four repeated measures outcomes: 1) post-crisis episode routine care utilization within 30 days; 2) post-crisis episode crisis service reutilization within 30 days; 3) post-crisis episode housing assessment within 30 days; and 4) post-crisis episode jail entry within 30 days. Routine care services will include receipt of outpatient services within 30-days following the index crisis episode in programs related to mental health, substance use, primary care, and integrated behavioral health in primary care. We will exclude residential programs and other services that are not intended to serve as routine care nor as a front-door crisis service. Acute care reutilization will include when an individual has a crisis care episode within 30-days following discharge from the index crisis episode. Housing assessment will be determined among those who are identified as PEH as having an HMIS record of receiving a housing assessment within 30-days following the index crisis episode. Finally, we will measure jail entry within 30-days following the index crisis episode based on clinical records from JIMS or Epic that are documented for every person who enters the San Francisco County Jail.

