### Program

The Behavioral Health Services division of the San Francisco Department of Public Health (SFDPH) has an extensive infrastructure for mental health and substance use disorder services, yet one important gap has remained: real-time response for people in behavioral health crisis in the streets. In 2019, San Francisco’s 9-1-1 call data indicates that approximately 50,000 behavioral health related calls were received, most of which were responded to by a law enforcement unit. Because most calls were not related to criminal events, and instead to mental health and social needs experienced by PEH, San Francisco behavioral health and governmental leaders worked with community stakeholders to create the SCRT to respond as an alternative able to be more responsive to behavioral health crises that happen on the street [16].

The SCRT was designed based on previous co-responder models [17, 18]. To meet the goal of diverting calls that would typically go to the San Francisco Police Department, this trauma-informed specialty behavioral health team is dispatched solely by 9-1-1 operators. The SCRT utilizes a co-responder model comprised of a behavioral health clinician, a paramedic from the San Francisco Fire Department and a peer specialist. Each team member plays a role in providing care including immediate stabilization of urgent medical need (paramedic), de-escalation of the crisis (behavioral health clinician) and person-centered peer support (peer specialist). The team triages clients to the appropriate level of care, be it through resolution of the crisis in the field, linkage to outpatient mental health and substance use services, or transport to an acute treatment setting. The SCRT was first piloted in San Francisco’s highest demand neighborhoods in December 2020 and then was incrementally expanded to be citywide by June 2021 (Fig 1).

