#### Study population

The SCRT aims to provide specialty mental health response and enhanced resources to adults in San Francisco who experience crises related to mental health and/or substance use disorders and are experiencing homelessness. Therefore, the study population will be defined based on age greater than 18 years, meeting criteria for homelessness in the 12 months prior to or 3 months following the crisis episode, and receipt of crisis care from any of San Francisco’s “front door” programs for people in an acute behavioral health crisis. These settings include two mobile crisis programs (Comprehensive Crisis Services and the SCRT), a crisis stabilization unit (DORE Urgent Care Clinic), and emergency psychiatric services (Zuckerberg San Francisco General Hospital’s Psychiatric Emergency Services [PES] and Emergency Department visits with a primary behavioral health diagnosis) (Fig 2). The population of housed adults utilizing acute behavioral health services will be utilized as a control group in the ITS sensitivity analyses.

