## Discussion

Many states and counties throughout the U.S. have turned to mobile crisis services as a potential cost-effective solution to constraints in behavioral health service capacity. A 2020 report issued by the Substance Abuse and Mental Health Services Administration, titled “National Guidelines for Crisis Care–A Best Practice Toolkit,” lays out essential services for a crisis continuum of care: call centers, mobile teams, and stabilization centers [38]. Programs such as SCRT are key to health systems seeking solutions to divert 9-1-1 calls away from law enforcement and instead to specialized behavioral health clinicians who can triage and link clients to an appropriate level of care. Further implementation science research is essential to grow the evidence base for effective mobile crisis models to help address the behavioral health needs of people experiencing a crisis, especially vulnerable populations such as people experiencing homelessness and health disparities.

The study described in this protocol exemplifies how implementation science methods can increase our understanding of the effectiveness and acceptability of mobile crisis response programs. By describing factors and mechanisms that facilitate or impede the effectiveness of SCRT in diverting clients from unnecessary additional crisis services or jail entry while improving linkage to routine care and housing services, this study will inform future strategies for implementing mobile crisis interventions into other settings. Additionally, the qualitative approaches will provide a nuanced understanding of how an intervention such as SCRT impacts the lives of adults experiencing homelessness in San Francisco and allow for more refined interpretation of the quantitative findings.

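### The jail outcome starts its clock only at a health-system crisis episode, so it can track jail entry among crisis-service users but cannot show whether SCRT diverts people from jail at the first 9-1-1 response

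*Protocol article*

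**What the plan says.** The Program section of the protocol article gives the background. Of about 50,000 behavioral health 9-1-1 calls in 2019, it describes the response as "most of which were responded to by a law enforcement unit". The team's purpose begins "To meet the goal of diverting calls that would typically go to the San Francisco Police Department", and it is "dispatched solely by 9-1-1 operators".

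Under Study population, a person enters the study by receiving care in a front-door setting. The list opens "These settings include two mobile crisis programs (Comprehensive Crisis Services and the SCRT), a crisis stabilization unit" and goes on to emergency psychiatric services and the emergency department. Police contact is not on it.

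Under Index crisis episode, the event that starts follow-up is "defined as the first instance in a given month that an individual has a crisis episode". Under Outcome variables, the jail measure is "4) post-crisis episode jail entry within 30 days", taken from jail clinical records "that are documented for every person who enters the San Francisco County Jail". Under Interrupted time series analysis, each outcome is a monthly proportion of the target population.

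The Discussion says the study will inform on the "effectiveness of SCRT in diverting clients from unnecessary additional crisis services or jail entry". The Limitations section notes that 9-1-1 dispatch data, which might identify the calls moved from police to SCRT, are unavailable. It does not connect this to the jail outcome.

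**The concern.** The response that SCRT replaces is largely a police contact, and a police contact does not open an index episode. SCRT contact does. The launch of the program therefore changes who is observed as well as how they are treated.

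Before December 2020, someone met by police and booked into jail, with no front-door episode in the preceding 30 days, is absent from both numerator and denominator. After launch, the same person met by SCRT joins the denominator, and a jail entry in the next 30 days is counted. The bookings that a police-alternative team might prevent at the moment of response are missing from the baseline.

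At stake is how one of the four main outcomes is read. A flat or rising series could be taken as failure to divert, and a falling one as success, when neither follows from what is measured.

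**Working it through.** The documents give no jail rate, caseload or power figure for this outcome, so there is no stated figure to reproduce. The check has two parts.

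**1. Definitions applied to the same 9-1-1 call**

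| | Before launch, police respond | After launch, SCRT responds |
|---|---|---|
| Opens an index episode? | No, unless the person also reaches a listed setting | Yes |
| In the monthly denominator? | Only through some other front-door episode | Yes |
| Jail entry counted? | Only if within 30 days after some other index episode | Yes, if within 30 days |

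The safeguards listed under Interrupted time series analysis do not restore the missing group. The pilot and non-pilot areas are compared on crisis episodes by zip code, and the housed controls are adults using crisis services. Both rest on crisis-service records. The example of a non-equivalent outcome concerns starting outpatient care, not jail.

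**2. Illustration (every input is an assumption)**

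- N0 = 600 existing index patients a month, with 30-day jail risk r0 = 10%, unchanged by the launch
- D = 200 people a month moved from police-only contact to SCRT
- j = their jail risk under a police response, 2% to 20%
- r1 = their 30-day jail risk after SCRT contact, 2% to 15%

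Measured baseline = r0. Measured post-launch = (N0·r0 + D·r1)/(N0 + D). All-comer baseline = (N0·r0 + D·j)/(N0 + D). Hence:

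- measured change = D(r1 − r0)/(N0 + D)
- all-comer change = D(r1 − j)/(N0 + D)
- difference, measured minus all-comer = D(j − r0)/(N0 + D)

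The measured change does not contain j, which is the quantity that first-response diversion is about. The two changes agree only when j = r0.

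| j | r1 | Measured change | All-comer change |
|---|---|---|---|
| 20% | 15% | 200 × 0.05/800 = +1.25 points | 200 × (−0.05)/800 = −1.25 points |
| 20% | 10% | 0.00 points | 200 × (−0.10)/800 = −2.50 points |
| 2% | 5% | 200 × (−0.05)/800 = −1.25 points | 200 × 0.03/800 = +0.75 points |
| 10% | 5% | −1.25 points | −1.25 points |

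**How much of the baseline could be unseen.** Take 1,000 front-door users a month with risk 5% or 10%, and 100, 250 or 500 people moved, whose risk goes from 20% to 15%, 15% to 12%, or 10% to 5%. The uncounted share of baseline jail entries runs from 10/(100 + 10) = 9% to 100/(50 + 100) = 67%.

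Total entries fall in all 18 combinations, while the planned proportion is unchanged or rises in 15. That count is not a likelihood. The number of people moved does not affect the sign, so there are only six distinct cases, and in five of them the SCRT-client risk was set at or above the front-door risk.

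**The case against.** The strongest reply is that the question is already restricted. The Abstract and the opening of Methods ask about homeless adults who use or present to crisis services, and the outcome is labelled as post-crisis. For that population the index-conditioned measure is coherent. The Discussion's phrase on jail entry is paired with additional crisis services and can be read as diversion after the encounter, which the series does address. This largely stands. What remains is that the Discussion does not say which kind of diversion it means, in a program whose purpose is to replace a police response.

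A second reply is that the Limitations section already discloses the missing dispatch data. It does, but it does not state the consequence for the jail outcome.

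A third is that the wrong-sign results are a case-mix effect. That is right: with the assumed inputs, restricting to the older entry points would leave a flat series. The omission would still remain, because j appears nowhere in the data.

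Three stronger readings might be inferred, and the documents do not support them:

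- *Police response is the study's comparator.* The protocol never says so. Its comparisons are between periods, between areas, and with housed crisis-service users.
- *Baseline jail entries from police contact are never counted.* They are counted when an index episode occurred in the prior 30 days. Police contacts that end in psychiatric emergency services, or in the emergency department with a primary behavioral health diagnosis, can enter the population. Jail encounters in the prior 12 months are a covariate.
- *The plan will understate SCRT's benefit.* The bias can go either way, and the documents give no rates from which to judge.

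**Conclusion.** The point holds in a limited form. The planned series can estimate 30-day jail entry among homeless users of crisis services, with a case mix that changes when SCRT starts. It cannot identify diversion from jail at first response, because the jail risk under a police response is not in the data for people without an index episode. This follows from the definitions alone and needs no assumed rate.

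Its size is unknown. With the inputs above, the measured change departs from the all-comer change by between 200 × (0.02 − 0.10)/800 = −2.0 and 200 × (0.20 − 0.10)/800 = +2.5 percentage points. Those figures show that the distortion can exceed the effect and reverse its sign; they do not predict what will happen. A reader might infer that the jail outcome is worthless. It is not: it answers a narrower question than jail diversion at the 9-1-1 response, and should be reported as such.

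**What to change.** 1. **Limit the conclusion.** Report the existing outcome as jail entry after a health-system crisis contact. State in the Discussion and Limitations that it does not measure diversion from jail at first response, and that the missing dispatch data are part of the reason. This costs a sentence or two.

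2. **Add a supplementary series.** Each month, take adults recorded as homeless in the prior 12 months from sources other than SCRT or its follow-up, where possible restricted to those with a prior behavioral health diagnosis. The numerator is those with a JIMS or Epic jail entry that month, whether or not a crisis episode came first. Analyse it with the same interrupted time series model. The records are already being linked and cover every jail entrant, so the cost is a second denominator, an additional model, and possibly a wider extract to include homeless adults without a crisis episode.

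The supplementary series has downsides that should be stated with it: dilution by arrests unrelated to behavioral health crises, omission of people known only through SCRT, and the October 2021 change of jail record system, which falls inside the full-implementation period. For these reasons it should be read beside the existing outcome and not serve as the sole basis for a diversion claim.

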#### Interrupted time series analysis

The ITS analysis will examine three periods: 1) Pre-SCRT baseline (November 2019 to November 2020), 2) SCRT partial implementation (December 2020 to July 2021), and 3) SCRT full implementation (August 2021 to August 2022). Each of the outcome measures will be computed as a monthly proportion, with the numerator equaling the number of individuals meeting criteria for each outcome and the denominator equaling the total target population in a given month. Using month-long time intervals would yield between 8 and 12 data points per time period, though the final interval length may change depending on the trade-offs between length of observation and statistical power.

Generalized estimating equations (GEE) will be used, with robust standard errors to account for within-person correlation [27], to analyze the trends in outcomes pre-implementation, during partial implementation, and after the implementation of SCRT. Models will include a variable for time (month) after the beginning of our observation period, a variable for time each time period subsequent to baseline, and the interaction between these variables to assess change in the trajectory of each outcome. Models will be adjusted by the covariates described above and interaction terms constructed to understand the relative effects of covariates and the ITS variables.

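### The 30-day crisis reutilization outcome counts SCRT contacts, which could not occur in the baseline period, so part of any rise may reflect a newly recorded service rather than more need

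*Protocol article*

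**What the plan says.** Four parts of the protocol article bear on this outcome.

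- **Outcome variables:** "Acute care reutilization will include when an individual has a crisis care episode within 30-days following discharge from the index crisis episode". No setting is listed or excluded.
- **Study population:** the crisis settings that define the cohort include "two mobile crisis programs (Comprehensive Crisis Services and the SCRT"), together with DORE Urgent Care, PES and emergency department (ED) visits with a primary behavioral health diagnosis. The Fig 2 caption also names SCRT as a crisis entry point.
- **Index crisis episode:** some sequences are classed as "a distinct crisis episode that mostly likely signifies reutilization (e.g., PES followed by mobile crisis, or two consecutive mobile crisis episodes"). For other sequences the authors will "combine sequences with a step up or down in service intensity that occur within two or fewer days", so that care transitions are not scored as reutilization. Mobile crisis followed by a facility is given as an example of a step-up.
- **Program and Interrupted time series analysis:** SCRT started in the "highest demand neighborhoods in December 2020 and then was incrementally expanded to be citywide by June 2021". The first segment is "Pre-SCRT baseline (November 2019 to November 2020").

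On what came before SCRT, the Program section says of about 50,000 behavioral health calls to 9-1-1 in 2019: "most of which were responded to by a law enforcement unit". The Limitations section says that dispatch data will not be available for the evaluation.

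**The concern.** An interrupted time series needs an outcome that is ascertained in the same way before and after the interruption. Here the list of countable events grows when the intervention arrives, because the intervention is itself one of the events. A person seen at PES and then by SCRT, or twice by SCRT, scores as a reutilization after December 2020. Neither sequence was possible before.

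Reutilization is one of four main outcomes, and reducing it is a stated goal of the follow-up service attached to SCRT. If the rate rises, the model cannot tell whether people returned to crisis care more often or whether a new service made some returns visible. If the rate stays flat, a real fall in returns to facilities may be hidden behind added SCRT contacts. The change phases in with the rollout, so it falls on the level and slope terms for the partial and full implementation segments, which carry the program effect.

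**Working it through.** The article states no reutilization rate, effect size or power figure for this outcome, so there is nothing to reproduce. The check is a comparison of definitions, followed by an illustration of size.

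**Step 1. Which return events can be scored in each period?**

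| Return event within 30 days | Baseline (Nov 2019 to Nov 2020) | From Dec 2020 |
|---|---|---|
| PES, ED with behavioral health diagnosis, DORE, Comprehensive Crisis Services | possible | possible |
| SCRT after PES | impossible | counts |
| SCRT after SCRT | impossible | counts |

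**Step 2. Do the planned safeguards remove the difference?** The Interrupted time series analysis section plans three.

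- *Pilot versus non-pilot zip codes.* The added events occur where SCRT is active, so the contrast between areas contains them.
- *Housed adults as a control in a difference of differences.* SCRT is aimed at people experiencing homelessness, so the added events fall mainly in the target group and do not cancel.
- *Non-equivalent outcomes, such as non-crisis entry to outpatient care.* These contain no SCRT contacts and cannot reveal the problem.

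The trajectory variable in Index crisis episode describes the entry and end points of the index episode, not the setting of the return.

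**Step 3. How large could it be?** Both inputs are assumptions, since the article gives neither:

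- r = 30-day return to settings that existed at baseline, held constant over time: 20%, 30%, 40%
- q = share of people with no such return who have an SCRT recontact within 30 days: 2%, 5%, 10%

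Measured rate after SCRT = r + (1 - r)q, so the apparent rise is (1 - r)q.

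| r | q = 2% | q = 5% | q = 10% |
|---|---|---|---|
| 20% | 0.80 x 0.02 = +1.6 points | +4.0 | +8.0 |
| 30% | 0.70 x 0.02 = +1.4 | +3.5 | +7.0 |
| 40% | 0.60 x 0.02 = +1.2 | +3.0 | +6.0 |

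The range is +1.2 to +8.0 points with no change in returns to any existing service.

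**Step 4. What does substitution do?** Suppose instead that a share v of the existing returns moves from a facility to SCRT. The all-contact rate does not change, because each person is still counted. A rate restricted to the older settings falls by r x v although nobody returned to crisis care less often. Neither version is sufficient alone.

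**Step 5. The two-day merge rule.** The rule is the same in all periods. What changes is that SCRT contacts start to pass through it. If e is the share of returns that fall within two days (10-20%) and f the share of index episodes that come to begin with SCRT (10-30%), all assumed, the measured rate falls by r x e x f: from 0.20 x 0.10 x 0.10 = 0.2 points to 0.40 x 0.20 x 0.30 = 2.4 points.

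**The case against.** The strongest reply is that counting every crisis contact answers a legitimate system-level question: did the person come back to crisis care at all? Removing SCRT from the outcome would score a person who relapses and is seen by SCRT instead of PES as a success, which favors the program by construction. This stands. It is a reason to report two versions, and it rules out replacing the all-contact version with the restricted one as the only main outcome.

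Three stronger readings are tempting, and the article does not support them.

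- *A reader might infer that repeat street crises before SCRT left no record.* The Program section says only that law enforcement answered most calls. It does not say where those people were taken. A police response that ended at PES, the ED or DORE would have been recorded and counted. The statement also covers all behavioral health calls, not returns within 30 days of an index episode.
- *A reader might infer that the merge rule itself changes at the intervention date.* It does not. It covers Comprehensive Crisis Services in the baseline too, and it stops an SCRT transport to a facility from being scored as reuse. What remains is narrower: as described, it would also absorb a facility visit within two days of an SCRT contact resolved in the field.
- *A reader might infer that any rise is an artefact of known size.* The rates in the working are assumed, and the +1.2 to +8.0 points allow no substitution. The merge rule works in the opposite direction, so the net effect on the measured rate cannot be signed from the article.

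It is also fair to say that the article models partial implementation as a separate segment and discloses the lack of dispatch data. Neither step makes the event list comparable across periods. Because the article itself fixes the outcome and the sequence rules, this is not a detail left to an analysis plan.

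**Conclusion.** The point holds for the numerator of the reutilization outcome. SCRT contacts count as return events, they cannot occur in the baseline segment, and none of the planned comparisons removes the difference. A rise after December 2020 cannot be read as more need for crisis care from this outcome alone.

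The size is unknown. It is about +1 to +8 percentage points under three assumptions: 20-40% return to existing settings, 2-10% added SCRT recontact among people without such a return, and no substitution. Substitution would shrink it. That SCRT counts as a return event follows from Study population, Index crisis episode and the Fig 2 caption read together; Outcome variables does not list the settings, and nothing in the article says otherwise.

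The all-contact definition is not wrong in itself. The fault is that it stands alone as the measure of reutilization.

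**What to change.** 1. Prespecify a reutilization outcome limited to settings that operated in all three periods: PES, ED with a primary behavioral health diagnosis, DORE and Comprehensive Crisis Services. The numerator artefact is then zero by construction.
2. Report it beside the all-crisis-contact version, and attribute a change in reutilization to SCRT only when both are shown. A flat restricted rate with a rising all-contact rate points to added SCRT contacts. A falling restricted rate with a flat all-contact rate points to substitution. A fall in both is what a real reduction would look like.
3. Add a sensitivity analysis of the two-day rule with a shorter or no merge window. Separating SCRT transports from contacts resolved in the field would be better if the records allow it, but neither Data sources and matching procedures nor Covariates lists a transport or hand-off field, so this should not be assumed.

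The cost is recoding returns by setting, one extra model and the merge sensitivity runs. The drawback is that the restricted version may favor SCRT where its contacts replace facility visits, which is why it should not be reported alone. The fix also leaves the denominator as it is: SCRT contacts can still be index episodes, so the mix of people entering the series may shift with the rollout.
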